## Abstract

**Background:**

Efficacy research has shown that intensive individual lifestyle intervention lowers the risk for developing type 2 diabetes mellitus and the metabolic syndrome. Translational research is needed to test real-world models of lifestyle interventions in primary care settings.

**Design:**

E-LITE is a three-arm randomized controlled clinical trial aimed at testing the feasibility and potential effectiveness of two lifestyle interventions: information technology-assisted self-management, either alone or in combination with care management by a dietitian and exercise counselor, in comparison to usual care. Overweight or obese adults with pre-diabetes and/or metabolic syndrome (n = 240) recruited from a community-based primary care clinic are randomly assigned to one of three treatment conditions. Treatment will last 15 months and involves a three-month intensive treatment phase followed by a 12-month maintenance phase. Follow-up assessment occurs at three, six, and 15 months. The primary outcome is change in body mass index. The target sample size will provide 80% power for detecting a net difference of half a standard deviation in body mass index at 15 months between either of the self-management or care management interventions and usual care at a two-sided α level of 0.05, assuming up to a 20% rate of loss to 15-month follow-up.

Secondary outcomes include glycemic control, additional cardiovascular risk factors, and health-related quality of life. Potential mediators (e.g., treatment adherence, caloric intake, physical activity level) and moderators (e.g., age, gender, race/ethnicity, baseline mental status) of the intervention's effect on weight change also will be examined.

**Discussion:**

This study will provide objective evidence on the extent of reductions in body mass index and related cardiometabolic risk factors from two lifestyle intervention programs of varying intensity that could be implemented as part of routine health care.

**Trial registration:**

NCT00842426

## Background

Diabetes mellitus affects nearly 24 million Americans (8% of the U.S. population), and type 2 diabetes accounts for about 90% to 95% of all diagnosed cases of diabetes [1,2]. The prevalence of diagnosed type 2 diabetes increased six-fold in the latter half of the past century [1,2]. This dramatic increase is largely attributed to the epidemics of obesity and physical inactivity [3]. About two-thirds of U.S. adults are overweight or obese [4], and 57 million people are estimated to have pre-diabetes -- a condition characterized by blood glucose levels that are higher than normal but not yet high enough to be diagnosed as diabetes. Overweight or obese individuals with pre-diabetes are at high risk for progression to diabetes. A vast majority of these individuals also have an increased risk of cardiovascular disease (CVD) because of concomitant risk factors, such as abdominal obesity, atherogenic dyslipidemia, and elevated blood pressure. The constellation of these common CVD risk factors is known as the metabolic syndrome [5].

The Diabetes Prevention Program (DPP) has demonstrated that an intensive lifestyle intervention focused on lifestyle changes and weight reduction can successfully prevent or delay the onset of type 2 diabetes and the metabolic syndrome in overweight or obese adults with pre-diabetes [6]. The DPP intervention required frequent, face-to-face, individual counseling [7]. Despite evidence of potential cost-effectiveness of the DPP intervention [8,9], the substantial resources required for its implementation are a significant barrier to widespread dissemination. A wide range of research has been underway related to translation of the DPP into real world settings, such as studies that assess cost-effective and generalizable methods of delivering evidence-based lifestyle modifications in small groups and over the Internet, as well as methods to sustain behavior change and weight loss [10-12].

Recently, the 16 "core curriculum" individual counseling sessions of the DPP intervention have been adapted for delivery in a 12 session group-based program called Group Lifestyle Balance (GLB)™ [13], and preliminary evaluations of the program have suggested potential effectiveness [14,15]. Past studies have shown that group interventions are similar in efficacy to individual interventions for weight loss [16,17] and may markedly improve intervention cost-effectiveness [8,9]. The Internet is another alternative mode of delivery of lifestyle interventions. Several randomized controlled trials have demonstrated the efficacy of Internet-based lifestyle interventions in overweight or obese individuals [18-20], including those at risk for type 2 diabetes [21].

To date, few studies have rigorously tested the feasibility and effectiveness of group- and Internet-based lifestyle interventions for weight management and risk reduction in primary care settings. Weight loss in overweight or obese patients with associated risk factors is of high priority for clinical care settings given the growing prevalence of obesity-related complications, and preventative health care is a major primary care goal. However, obesity and risk factor management has thus far been largely a failure in primary care settings throughout the United States [22,23]. Research is needed to translate efficacious lifestyle interventions into primary care practice, and in the process, evaluate their cost-effectiveness, generalizability, and sustainability.

### Aims

The present study aims to evaluate the feasibility and potential effectiveness of two lifestyle interventions, information technology-assisted self-management alone (the SM intervention) or SM combined with care management by a dietitian and exercise counselor (the CM intervention), in comparison to usual care (UC). The primary hypothesis for each intervention (SM and CM) is that intervention participants will achieve greater reductions in body mass index (BMI) than UC participants at 15 months. Secondary research goals include comparing the effects of each intervention to UC on changes in glycemic control (fasting blood glucose and hemoglobin A1c), additional cardiovascular risk factors (serum lipids, blood pressure, waist circumference, and C-reactive protein [CRP]), health-related quality of life and psychosocial well-being. Differences between CM and SM intervention effects on weight loss and secondary outcomes also will be examined. Potential mediators (e.g., treatment adherence, caloric intake, physical activity level) and moderators (e.g., age, gender, race/ethnicity, baseline mental status) of the intervention effects on weight change and secondary outcomes will be explored. Additionally, process measures will be evaluated to assess the extent of participation of patients in each intervention and the potential reach, adoption, implementation and maintenance of the interventions in primary care practice.

## Methods/Design

### Study Design

E-LITE is a randomized controlled clinical trial in which overweight or obese adults with an increased risk for CVD and diabetes are equally randomized to one of three arms: UC (control), SM, or CM. All procedures and materials were approved by the Palo Alto Medical Foundation Research Institute's Institutional Review Board.

### Eligibility Criteria

Participants are recruited from a primary care health center of the Palo Alto Medical Foundation (PAMF), a community-based multi-specialty group practice in California. Primary care patients ages 18 years and older who are overweight or obese and have pre-diabetes and/or metabolic syndrome are eligible to participate. Exclusion criteria are designed to: 1) avoid potential contamination and minimize confounding; 2) minimize safety concerns; and 3) prevent poor adherence and loss to follow-up. Table 1 enumerates the inclusion and exclusion criteria.

**Table 1 T1:** Participant inclusion and exclusion criteria

**Inclusion criteria**
1. Ethnicity: All ethnic groups;
2. Gender: Men and Women;
3. Age (as of date of enrollment):
a). Lower age limit: 18 years;
b). Upper age limit: NONE (*only exclude for cause, e.g. diseases, functional limitations detailed below*);
4. Body mass index ≥ 25.0 kg/m^2^;
5.Having pre-diabetes and/or metabolic syndrome based on the following criteria:
a). Pre-diabetes: fasting plasma glucose between 100 and 125 mg/dL;
b). Metabolic syndrome: Three or more of the following:
--Waist circumference ≥ 40 inches in men; ≥ 35 inches in women (if in Asian American ≥ 35 inches in men; ≥ 31 inches in women);
--Triglycerides ≥ 150 mg/dL;
--High-density lipoprotein cholesterol (HDL-C) < 40 mg/dL in men; < 50 mg/dL in women;
--Systolic blood pressure ≥ 130 mm Hg or diastolic blood pressure ≥ 85 mm Hg;
--Fasting plasma glucose between 100 and 125 mg/dL.
6. Having a primary care physician (PCP);
7. Able and willing to enroll and provide written, informed consent, i.e., to: 1) meet the time and data collection requirements of the study; 2) be randomized to one of the three intervention arms; 3) adhere to the recommendations of the study intervention as assigned; 4) participate in follow-up for 12 months; and 5) allow extraction of relevant information from their medical records.
**Exclusion criteria**
1. Inability to speak, read or understand English;
2. No regular access to a computer with Internet and email capabilities;
3. Triglycerides ≥ 400 mg/dL;
4. Systolic blood pressure ≥ 160 mm Hg or diastolic blood pressure ≥ 100 mm Hg;
5. Initiation or change of drug therapy for elevated blood pressure or abnormal lipid levels within the past 3 months;
6. Initiation or change of antidepressant medication within the past 3 months;
7. Having a medical or physical condition that make moderate intensity physical activity (like a brisk walk) difficult or unsafe;
8. Use of weight-loss medications in the past 3 months;
9. Regular use (> 5 days/month) of medications that affect appetite or weight (e.g., oral corticosteroids, insulin, oral hypoglycemics etc.);
10. Currently enrolled in a lifestyle intervention program at PAMF or elsewhere;
11. Planning to undergo bariatric surgery during the study period;
12. Diagnosis of Type 1 or Type 2 diabetes mellitus;
13. Significant medical co-morbidities, including uncontrolled metabolic disorders (e.g., thyroid, renal, liver), heart disease, stroke, and ongoing substance abuse;
14. Renal insufficiency (i.e. glomerular filtration rate < 60 mL/min/1.73 m^2^)
15. Diagnosis of psychiatric disorders that would limit adequate informed consent or ability to comply with study protocol;
16. Diagnosis of cancer (other than non-melanoma skin cancer) that was active or treated with radiation or chemotherapy within the past 2 years;
17. Diagnosis of a terminal illness and/or in hospice care;
18. Pregnant, lactating or planning to become pregnant during the study period;
19. Already enrolled or planning to enroll in a research study that would limit full participation in this study or confound the observation and interpretation of the study's findings;
20. Family/household member of another study participant or of a study staff member;
21. No longer a PAMF patient or planning to transfer care outside of PAMF during the study period;
22. Planning to move out of the area during the study period;
23. PCP determination that the study is medically inappropriate or unsafe for the patient;
24. Investigator discretion for clinical safety or protocol adherence reasons.

### Recruitment and Screening Process

Target sample size for E-LITE is 240, recruited in three sequential cohorts. The screening process for each cohort begins with identification using relevant data available in the patient's electronic health record of age-appropriate, potentially eligible patients whose primary care provider (PCP) regards the interventions under study to be medically appropriate and safe for that patient. Patients whose participation is approved by their PCP are asked to complete a brief questionnaire regarding major exclusions, either online or by phone. Those who pass the initial screen are scheduled for a formal eligibility determination (baseline) visit (BV1), and, within two weeks prior to the visit, they are contacted and given instructions for completion of an online baseline questionnaire.

The BV1 occurs no more than four months after the initial screen and no more than four weeks prior to randomization. It includes completion of additional eligibility questionnaires, measurement of height, weight, waist circumference, and resting blood pressure, and a fasting blood draw for tests of plasma glucose and lipids at the onsite Clinical Laboratory. Time permitting, a seven-day physical activity recall [24] is completed; otherwise, it will be completed at the baseline assessment/randomization visit (BV2). Participants are given instructions and a three-day food record form to be completed and returned at BV2. Participants who have possible angina or peripheral vascular disease based on the Rose Questionnaire [25] are referred to their PCP for further evaluation and may only continue with explicit authorization of their physician.

Participants who are eligible to continue on the basis of BV1 are scheduled for BV2, which occurs at least seven days after BV1 and no more than three weeks prior to the start of the intervention. The BV2 includes measurement of weight, waist circumference, and resting blood pressure, a review of the three-day food record for completeness, complete review of medication and supplement use, a non-fasting blood draw for tests of A1c and CRP, and if necessary, completion of the physical activity recall. Following the measurements, participants are randomized.

All participants are properly and adequately informed and give appropriate consent at each step in the screening process of the trial and prior to participating in the post-randomization phase.

### Randomization and Blinding

Participants are randomized on a 1:1:1 basis to one of three arms: UC, SM, or CM. Pocock's "minimization" procedure [26] is used to assure better than chance group balance with respect to participant age, gender, race, BMI, fasting blood glucose, waist circumference, and use of PAMFOnline, which is PAMF's online patient portal to access his or her own health record (user vs. non-user). For each participant about to be randomized, a computerized randomization algorithm automatically calculates an imbalance score for each of the balancing factors, as the excess or deficit of previously randomized participants in each arm matching the current patient on that factor. These scores are summed over factors to form a total imbalance score, S, for each treatment arm. The randomization probability of assigning the patient to the treatment associated with the smallest S is set to 2/3, and the other two treatments are each assigned a probability of 1/6 based on Efron's biased coin method [27].

A designated research staff member who is not involved in follow-up data collection or data analysis assigns each study arm a non-revealing label, e.g., A, B, or C, and performs actual randomization of the participants. These labels are used in all study documents and other materials to ensure blinding of the investigators and staff responsible for follow-up data collection and analysis to participant treatment assignments throughout the trial.

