### Sample Size Considerations and Statistical Analysis

#### Sample Size

Given the target sample size of 240, we expect approximately 80% power for detecting a net difference of 1/2 of a standard deviation (equivalent to a medium effect size of 0.5) in BMI at 15 months between the SM intervention and usual care (and similarly, between the CM intervention and usual care) at a 2-sided α level of 0.05, assuming up to a 20% rate of loss to follow-up. The effect size is estimated based on a number of successful lifestyle weight loss intervention studies [6,18-20]. The power estimate was calculated based on a t-test using simplified assumptions. Note that the t-test calculation is conservative because it does not account for variance reduction due to adjustment for baseline variables, nor for the better than chance comparability of the experimental groups. The primary comparisons of each intervention with usual care will be conducted using two-sided procedures at the overall significant level of 0.05. Multiplicity adjustments are not necessary because the primary interest is to estimate separate treatment effects for a limited number (i.e., n = 2) of key contrasts that pertain to different interventions [53]. Therefore, p-values of each comparison will be compared to type I error α = 0.05 for significance.

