### Data Analysis

The primary hypothesis compares BMI between each intervention (SM and CM) and usual care at 15 months using an intent-to-treat analysis. Linear mixed modeling,

using SAS PROC MIXED [54] will test time and group interactions to asses whether within-subject change in BMI differs by condition. This basic analytical strategy also accounts for the nature of repeated measurements, the blocked design by cohorts, and the clustering of patients within physicians. The same analysis strategy is appropriate for evaluating secondary aims where the hypotheses are identical but with different outcome measures (e.g., glycemic control, other component risk factors of the metabolic syndrome, and psychosocial well-being). The longitudinal effects of the interventions will be assessed using the same model, except that the focus is comparisons within intervention groups at different time points. Analyses will also be conducted to examine whether there is a dose-response relationship between intervention adherence and outcome, where dose is defined in terms of number of group sessions attended, number of secure messages sent, number of self-monitoring logs, average daily intakes of calories and fat, and average number of minutes of physical activity per week.

For participants with missing outcomes at the primary (15-month) or secondary (3- and 6-month) assessment point, we will conduct and report on sensitivity analyses in which different imputation methods are used (e.g., the baseline-observation-carried-forward method, the "hot deck" procedure, and an appropriate multiple imputation method [55,56].

We will use the MacArthur approach, which modified the Baron & Kenny criteria, for defining moderators and mediators in clinical research studies [57]. Let T be the treatment, M be the potential moderator or mediator, and O be the outcome. Association between T, M, and O is examined using the following models:(1)

M is a moderator of the effect of T on O if M precedes T, γ_1 _= 0, and β_3 _≠ 0. M is a mediator of the effect of T on O if T precedes M, γ_1 _≠ 0, and either β_2 _≠ 0 or β_3 _≠ 0.

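### The mixed model does not name the minimization factors as covariates, so its standard errors do not recognise the balance and tests are somewhat conservative

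*Protocol article*

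**What the plan says.** **Allocation (Protocol article, Randomization and Blinding).** "Participants are randomized on a 1:1:1 basis to one of three arms: UC, SM, or CM". Minimization "is used to assure better than chance group balance with respect to participant age, gender, race, BMI, fasting blood glucose, waist circumference, and use" of the patient portal. The coin is biased: "The randomization probability of assigning the patient to the treatment associated with the smallest S is set to 2/3", and each of the other two arms gets 1/6.

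**Model (Data Analysis).** The primary analysis is a linear mixed model that tests time-by-group interactions on within-subject BMI change. The design features it is said to account for are "the nature of repeated measurements, the blocked design by cohorts, and the clustering of patients within physicians". The secondary outcomes use the same strategy. No baseline covariate is listed.

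**Power (Sample Size).** "Given the target sample size of 240, we expect approximately 80% power for detecting a net difference of 1/2 of a standard deviation". The difference refers to month-15 BMI, each intervention against control, and the calculation is set "at a 2-sided α level of 0.05, assuming up to a 20% rate of loss to follow-up". The section calls this t-test calculation conservative on two grounds: it leaves out the variance reduction from adjusting for baseline variables, "nor for the better than chance comparability of the experimental groups".

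**The concern.** Minimizing on prognostic factors reduces the true sampling variance of the difference between arms. A model without those factors keeps their variance in the residual, so its standard error describes a more variable estimate than the design produces. Intervals come out too wide and the test rejects a true null less often than 5%.

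The article also does not line up with itself. Sample Size anticipates baseline adjustment as a reserve of precision, but Data Analysis, which does list cohort and physician, does not say where that adjustment happens. At stake are calibration and some power, for the primary comparison and for every secondary outcome analysed the same way.

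**Working it through.** **1. The plan's own figure.** 240/3 = 80 per arm; 80 × 0.8 = 64 evaluable. A two-sample t-test with 64 per arm, a difference of 0.5 SD and two-sided α = 0.05 has power 0.801 (noncentral t; 0.807 by the normal formula). The stated 80% reproduces, with no credit for balance or adjustment.

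**2. What adjustment could add.** Let R² be the share of variance in the analysed outcome (here BMI change) explained by the factors. The article gives no value, so a range is assumed. Adjustment multiplies the SD by √(1 − R²), and power is recomputed with effect 0.5/√(1 − R²) at 64 per arm.

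| R² (assumed) | √(1 − R²) | Power |
|---|---|---|
| 0 | 1.000 | 0.801 |
| 0.05 | 0.975 | 0.821 |
| 0.10 | 0.949 | 0.841 |
| 0.20 | 0.894 | 0.881 |
| 0.30 | 0.837 | 0.918 |

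Not all of this is lost without adjustment, because balance already shrinks the true spread of the unadjusted estimate. Simulation is needed to separate the two.

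**3. Simulation of the stated scheme.** Three arms, 2/3–1/6–1/6 coin, 240 patients, 20% random loss, 2,500 trials per cell. Assumed: seven binary factors with equal effects, outcome SD 1. One intervention is compared with usual care by least squares on a single outcome, without and with the factors.

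| R² | Model SE, unadjusted | True SD, unadjusted | Type I error, unadjusted / adjusted | Power, unadjusted / adjusted |
|---|---|---|---|---|
| 0 | 0.177 | 0.181 | 5.4% / 5.6% | 0.808 / 0.803 |
| 0.05 | 0.177 | 0.172 | 4.9% / 5.3% | 0.803 / 0.810 |
| 0.10 | 0.177 | 0.170 | 3.9% / 4.2% | 0.807 / 0.823 |
| 0.20 | 0.177 | 0.166 | 3.5% / 5.3% | 0.814 / 0.874 |
| 0.30 | 0.177 | 0.155 | 3.0% / 4.7% | 0.826 / 0.914 |

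Monte Carlo error on type I error is √(0.05 × 0.95/2500) ≈ 0.4 points. The unadjusted SE is too large by 0.177/0.170 − 1 ≈ 4%, 0.177/0.166 − 1 ≈ 7% and 0.177/0.155 − 1 ≈ 14% at R² of 0.10, 0.20 and 0.30. Power forgone is 0.823 − 0.807 = 1.6 points, 0.874 − 0.814 = 6.0 points and 0.914 − 0.826 = 8.8 points. Unadjusted power is at least 0.80 throughout.

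**4. Baseline BMI.** As the baseline repeated measure it already does most of its work. If r is the correlation between baseline and 15-month BMI, the SE relative to a follow-up-only comparison is √(2(1 − r)) for change and √(1 − r²) for full baseline adjustment. At assumed r = 0.8, 0.9 and 0.95, change gives 0.63, 0.45 and 0.32, within about 5%, 3% and 1% of full adjustment. What is at issue is mainly the other six factors.

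**5. Which adjustment works.** The tested quantity is a time-by-group contrast. With baseline in the response, a factor effect that is constant over time cancels from within-subject change. In a random-intercept model fitted to complete simulated data, adding the factors as main effects left the 15-month interaction estimate (0.0943) and its SE (0.0859) unchanged to four digits. Factor-by-time terms, or baseline as a covariate, are needed.

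**The case against.** The strongest reply is that a condensed article need not list covariates, that Data Analysis describes only a basic strategy, and that Sample Size already foresees baseline adjustment; silence is not exclusion. That is fair as far as it goes, and a full analysis plan may settle it. What remains is visible in the article: it itemises the design features the model accounts for, down to cohort and physician, and leaves out the allocation method that it relies on elsewhere.

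A second reply is that only the variance in BMI change counts, and the factors may explain little of it. This stands. At 5% or less there is nothing to see beyond simulation error, and the larger figures need 20% to 30%.

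A reader might infer more than the article supports:

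- That all seven factors are left out. Baseline BMI is in the model as a repeated measure, and waist and glucose likewise enter as their own baselines when they are the outcome.
- That the power figure spends the gain from balancing. It does not: the 80% reproduces without it, and the gain is cited only as reserve.
- That the precision is lost entirely. The estimate is still less variable; the standard error fails to show it.
- That the trial risks false positives. The error runs the other way.

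**Conclusion.** The point holds as a modest, conservative miscalibration and a mismatch between Sample Size and Data Analysis. If the model is fitted as written and the factors explain 10% to 30% of the variance in BMI change, the standard error is about 4% to 14% too large, type I error is about 3% to 4%, and roughly 2 to 9 points of power are forgone. At 5% or less the effect is negligible. The sample size is not undermined and no false-positive inflation follows.

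The figures rest on an R² that the article does not give, on seven equally prognostic binary factors, on random loss, and on reading the half-SD effect in units of the SD of the analysed change. If that SD is instead the SD of BMI itself, a change analysis at an assumed r of 0.8 or more already has power of about 0.99. Little power is then left to lose, and the cost for the primary outcome is mainly interval width. Because the simulation leaves all seven factors unmodelled, it is an approximation for the BMI model, where baseline BMI is already present.

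**What to change.** In Data Analysis, model BMI at 3, 6 and 15 months with baseline BMI and the other six minimization factors (age, gender, race, fasting glucose, waist circumference, portal use) as covariates, keeping continuous factors on their continuous scale. If baseline BMI stays in the response, include factor-by-time terms, since main effects alone leave the tested contrast essentially unchanged. Do the same for each secondary outcome with its own baseline. State that this is the baseline adjustment that Sample Size refers to.

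The cost is analysis wording and a few degrees of freedom. All the factors are needed at allocation, so no new data are required. Naming them before unblinding also removes discretion over which baseline variables are meant.
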